## Donafenib tablets (referred to as donafenib)

Tyrosine kinase-mediated signaling is directly related to tumor occurrence and development. The development of drugs targeting this pathway has become a current hotspot in antitumor therapy. The successive successful market launch of various small molecule tyrosine kinase inhibitors (TKIs) strongly supports the antitumor pathway targeting tyrosine kinases. Receptor tyrosine kinase inhibitors include both single-target and multi-target TKIs. The early marketed protein kinase inhibitors were mainly specific inhibitors targeting a single target. Although they achieved remarkable success in tumor treatment upon their initial launch, the cellular signaling process is extremely complex. Attempting to block all signaling pathways of tumor cells through single-target drugs may not yield objective efficacy and could potentially lead to resistance, thus giving rise to the concept of multi-target drugs. Currently, research on multi-target receptor tyrosine kinase inhibitors is very active, among which sorafenib (abbreviated as: sorafenib) and malate sunitinib (abbreviated as: sunitinib) have been approved for marketing in the United States, becoming representatives of broad-spectrum TKIs.

Donafenib tablets are an oral multi-target multi-kinase inhibitor class of small molecule anti-tumor drugs developed by Suzhou Zelgen Biopharmaceutical Co., Ltd. Donafenib employs a novel and unique drug chemistry technique, forming a new structure by replacing a methyl group on the sorafenib molecule with a tri-deuterated methyl group. The deuteration rate is not less than 99.0%, and the deuterated compounds retain the basic physicochemical properties of the parent drug. At the same time, its metabolic stability may enhance pharmacological effects and will not lead to new toxic target organs and toxic effects caused by traditional chemical modifications. Donafenib has multiple targets and dual anti-tumor effects; it can directly inhibit the proliferation and growth of tumor cells by blocking the cell signaling pathway mediated by serine-threonine kinase (Raf/MEK/ERK), and it can also indirectly inhibit tumor cell growth by blocking the formation of new blood vessels in tumors through the inhibition of the activity of various tyrosine kinases such as vascular endothelial growth factor receptor (VEGFR) and platelet-derived growth factor receptor (PDGFR), becoming the first domestically produced targeted new drug for first-line treatment of advanced liver cancer to be marketed in China. In addition, Donafenib can also improve the tumor immune microenvironment through various mechanisms. Therefore, the combination of PD-1/PD-L1 antibodies with donafenib not only produces an additive effect but can also create a synergistic effect where 1+1>2, enhancing efficacy. For details, see the donafenib investigator's brochure (IB).

### 1.3.1 Preclinical studies of donafenib

#### 1.3.3.1 Pharmacokinetics

Beagle dogs were simultaneously administered 5.0 mg/kg of sorafenib and donafenib raw material via gavage [50% polyethylene glycol (PEG) 400/50% propylene glycol formulation], and both exhibited similar pharmacokinetic (PK) characteristics in beagle dogs, with peak plasma concentration time (T _max_ ) of approximately 1.7 hours; The peak concentration (C _max_ ) and AUC _0-t_ of donafenib are 101.9% and 112.5% of those of sorafenib, respectively, and the elimination half-lives (t _1/2_ ) of sorafenib and donafenib are 4.08 and 4.29 hours, respectively, with donafenib being 105% of sorafenib.

#### 1.3.3.2 Toxicology

1.3.3.2.1 Acute toxicity test

Wistar rats were administered a single oral dose of donafenib, with a maximum tolerated dose (MTD) greater than 2000 mg/kg. Beagle dogs were administered a single oral dose of donafenib, with an MTD greater than 1000 mg/kg;

1.3.3.2.2 Long-term toxicity study

Wistar rats were administered donafenib by oral gavage for 4 weeks. The target organs/systems for donafenib toxicity were the kidneys, hematopoietic system, immune system, digestive system, endocrine system (adrenal gland, thyroid), reproductive system, vasculature, and skeleton. No adverse reaction dose levels (NOAEL) were observed below 3 mg/kg, with the maximum tolerated dose (MTD) being 10 mg/kg. Beagle dogs were administered donafenib by oral gavage for 4 weeks. The target organs/systems for donafenib toxicity were the liver, adrenal gland, reproductive system (testes, epididymis, ovaries, uterus), and mesenteric lymph nodes, and it could cause damage to teeth and gums. Moreover, this trial failed to identify the NOAEL for donafenib , with the highest no severe toxicity dose (HNSTD) being 10 mg/kg.

The results of the 6-month long-term toxicity study showed that Wistar rats administered donafenib via oral gavage for 6 months had the toxicity target organs/systems including the kidneys, hematopoietic system, skeleton and teeth, adrenal glands, and male reproductive system (testes, epididymis). The HNSTD was 1.0 mg/kg. Beagle dogs administered donafenib via oral gavage for 6 months had the toxicity target organs including the liver, skin, teeth, and thymus, and could also induce anemia in the body. The HNSTD was 3 mg/kg;

1.3.3.2.3 Fertility and Early Embryonic Development Toxicity Test

Wistar rats were administered donafenib via oral gavage, with the NOAEL for male fertility being 3.0 mg/kg, and the NOAEL for female fertility and early embryonic development being 0.8 mg/kg;

New Zealand rabbits were administered toluenesulfonic acid donafenib via oral gavage, with the NOAEL for parental pregnant rabbits being less than 0.15 mg/kg; the NOAEL for embryos and fetuses was 0.15 mg/kg.

1.3.3.2.4 Mutagenicity Test

The Ames test result for donafenib was negative. The in vitro CHL cell chromosome aberration test result for donafenib was positive. The mouse bone marrow micronucleus test result was negative.

Detailed preclinical study results of donafenib can be found in the donafenib investigator's brochure.

### 1.3.2 Clinical Research of Donafenib

#### 1.3.2.1 Study TG1219DTT

The study TG1219DTT has been completed, with the objective of observing the safety and tolerability characteristics of different oral doses of donafenib tablets in humans, as well as monitoring the potential occurrence of DLT and maximum tolerated dose (MTD), pharmacokinetic parameters in the set dose groups, and providing a basis for the dosing regimen in the Phase II clinical trial. The trial includes three parts: a dose-escalation tolerance study, a pharmacokinetics study, and a study on the effect of food on drug metabolism. A total of 25 subjects with advanced malignant solid tumors were enrolled. Three patients in the 50 mg group participated only in the single-dose tolerance trial. In the single/multiple dose study, 22 patients participated, with sample sizes for each dose group being 3 for the 0.1 g group, 6 for the 0.2 g group, 7 for the 0.3 g group, and 6 for the 0.4 g group. Among the 22 patients in the single/multiple dose study group, 4 patients did not complete the planned 28-day dosing period due to adverse events, including 1 in the 0.2 g group, 2 in the 0.3 g group, and 1 in the 0.4 g group.

Safety study results: A total of 5 patients experienced DLT in this study, including 1 case in the 0.2g dose group, 1 case in the 0.3g dose group, and 3 cases in the 0.4g dose group. During the study period of single and multiple administrations, a total of 20 cases (80.0%) experienced adverse reactions (ADR). The incidence of ADR during the single administration phase was 36.0% (9/25), while the incidence of ADR during the multiple administration phase was 86.4% (19/22). Ranked by incidence, the most common adverse reactions were hand-foot syndrome (12 cases, 48.0%), diarrhea (8 cases, 32.0%), rash (6 cases, 24.0%), alopecia (5 cases, 20.0%), nail pigmentation (5 cases, 20.0%), and hypertension (5 cases, 20.0%). According to the classification by system organ, the 'gastrointestinal system' is the most common adverse reaction, with a total of 16 out of 25 patients (64.0%) experiencing 'gastrointestinal system' related adverse reactions. The main manifestations include diarrhea (8 cases, 32.0%), stomatitis (4 cases, 16.0%), reduced food intake (3 cases, 12.0%), nausea (2 cases, 8.0%), abdominal distension (2 cases, 8.0%), constipation (2 cases, 8.0%), and abdominal pain (2 cases, 8.0%). Fifteen patients (60.0%) experienced 'skin and subcutaneous tissue' related adverse reactions. The main 'skin and subcutaneous tissue' adverse reactions were hand-foot syndrome (12 cases, 48.0%), rash (6 cases, 24.0%), alopecia (5 cases, 20.0%), and nail pigmentation (5 cases, 20.0%), among others.

PK studies indicate that a single administration of donafenib , within the dose range of 0.1 to 0.4 g, results in an increase in the AUC _0-t_ and C _max_ of the parent drug in subjects as the administration dose increases, with the increase of the parent drug being generally consistent with the proportional increase in dose; the PK parameters of donafenib exhibit considerable inter-subject variability. donafenib was administered continuously, twice daily (Bid), for 28 days. During days 7 to 14 of administration, the plasma concentrations of donafenib and its metabolites reached a steady state. The ratio of the AUC _0-12h_ of donafenib on day 28 to that on day 1 (accumulation ratio) was 2.94 to 7.75, indicating a degree of accumulation. Within the dose range of 0.1 to 0.4 g, the AUC _0-12h,ss_ and C _max_ of donafenib did not show significant changes with increasing doses. A high-fat diet had little effect on the PK parameters of donafenib .

21 subjects completed at least one efficacy evaluation [according to the Response Evaluation Criteria in Solid Tumors (RECIST) v1.1]. 13 subjects entered the extended treatment period. There were 2 cases of subjects (9.5%) who achieved partial response (PR) [1 case of colorectal adenocarcinoma (0.3 g group), and 1 case of hepatocellular carcinoma (0.2 g group)], 10 cases of stable disease (47.6%) [3 cases of liver cancer (1 case each from the 0.1, 0.3, and 0.4 g groups), 4 cases of lung cancer (2 cases from the 0.2 g group, and 1 case each from the 0.1 g and 0.4 g groups), 2 cases of renal cancer (1 case each from the 0.1 g and 0.2 g groups), and 1 case of colorectal cancer (0.4 g group)], and 9 cases of disease progression (42.9%). Additionally, the tumor tissues of the tumor subjects exhibited significant cavitary necrosis, indicating that donafenib has a notable anti-angiogenic effect. Among the subjects in the extended trial period, the longest duration of medication was 17.8 months, the shortest was 3.0 months, and the average duration of medication was 7.9 months, with a 95% confidence interval (CI) of (5.0, 10.9). Among them, 3 cases (2 cases of renal cancer and 1 case of hepatocellular carcinoma) had a duration exceeding 12 months.

#### 1.3.2.2 Study ZGDH1B

Study ZGDH1B has been completed, with the primary objective of observing the safety and tolerability of donafenib tablets for liver cancer treatment at a clinically recommended dose in a larger sample. The study employed a randomized, open-label, parallel-group controlled design. A total of 106 subjects were planned for enrollment, with 107 subjects actually enrolled. The trial is designed with two groups: the donafenib tablet 0.2g group, with a total of 53 subjects; and the donafenib tablet 0.3g group, with a total of 54 subjects. Subjects will take the medication on an empty stomach, twice daily, with each treatment cycle lasting 4 weeks (28 days), until disease progression or intolerability occurs. Follow-up will occur once every cycle (4 weeks), and imaging efficacy evaluations will be conducted every two cycles (8 weeks).

Donafenib tablets demonstrated preliminary efficacy, with an objective response rate (ORR) of 7.8% (4 cases of PR) in the donafenib 0.2 g group, and a 95% confidence interval (CI) of 2.0% to 19.0%; The ORR for the 0.3 g group was 5.7% (3 cases of PR), with a 95% CI of 1.0% to 16.0%. In the 0.2 g group, a total of 33 cases (64.7%) experienced tumor progression, with a median time of 3.8 months (3.61-5.65); In the 0.3 g group, a total of 39 cases (73.6%) experienced tumor progression, with a median time of 3.7 months (2.04-5.52). The median overall survival in the 0.2 g group was 12.2 months (8.11-14.00); The median overall survival in the 0.3 g group was 10.3 months (7.10-15.90).

In terms of PK, the 0.2 g group received Bid continuous administration for 28 days, with a peak blood concentration of donafenib reached at 2.00 hours (median), C_max_ was 6.81 µg/mL, C_min_ was 2.20 µg/mL, and the plasma exposure AUCss was 46.7 h*µg/mL. C_max_ is 4.74 times that of Day 1 administration, and AUCss is 4.99 times that of Day 1 administration. In the 0.3g donafenib group, Bid continuous administration for 28 days resulted in a peak plasma concentration (median) of 9.13µg/mL at 2.00 hours, with C_max_ of 9.13µg/mL, C_min_ of 2.69µg/mL, and plasma exposure AUCss of 58.9h*µg/mL. C_max_ is 2.96 times that of Day 1 administration, and AUCss is 3.10 times that of Day 1 administration.

Safety profile, the incidence of TEAE in the 0.2g group is 96.2%, and in the 0.3g group is 98.1%; The incidence of SAE in the 0.2g group is 39.6%, and in the 0.3g group is 22.2%; The incidence of TEAE leading to death in the 0.2g group was 15.1%, and in the 0.3g group was 13.0%; The most frequently occurring SOC of TEAE in both groups was 'Skin and Subcutaneous Tissue Disorders' (incidence in the 0.2g group was 75.5%, and in the 0.3g group was 83.3%), with the PT being Palmoplantar Erythrodysesthesia Syndrome (incidence in the 0.2g group was 62.3%, and in the 0.3g group was 61.1%). The overall safety and tolerability of donafenib 0.2g and 0.3g were good.

**1.3.2.3 Study ZGDH3**

The open, randomized, parallel-controlled, multicenter phase II/III clinical study (ZGDH3) of donafenib as first-line treatment for advanced hepatocellular carcinoma included a total of 668 unresectable advanced HCC patients, randomized 1:1, receiving donafenib 0.2g BID or Sorafenib 0.4g BID treatment. The results showed that the OS in the donafenib group was significantly prolonged compared to the Sorafenib group (12.1 months vs 10.3 months; HR=0.831; 95% CI, 0.699~0.988). donafenib demonstrated better tolerability compared to Sorafenib: the incidence of ≥3 grade adverse events (AE) (57.4% vs 67.5%, *p* =0.0082), ≥3 grade drug adverse reactions (ADR) (37.5% vs 49.7%, *p* =0.0018), and the incidence of ADR leading to drug suspension and dose reduction (30.3% vs 42.5%, *p* =0.0013) were all significantly lower than those of Sorafenib; The incidence and severity of hand-foot skin reactions, liver function abnormalities, and diarrhea were all lower than those in the sorafenib group. In the treatment with a single anti-angiogenic targeted drug, donafenib is the only targeted drug to date that has shown superior overall survival (OS) compared to sorafenib in head-to-head studies for advanced HCC ^[10]^.

**1.4 Recombinant humanized anti PD-1/PD-L1 monoclonal antibody**

PD-1 is an immunosuppressive receptor primarily expressed on the surface of T cells, B cells, monocytes, and NK cells, with its corresponding ligands being programmed death ligand-1 (PD-L1) and programmed death ligand-2 (PD-L2). Among them, PD-L1 is widely expressed in various tumor cells and immune cells, and its expression level can be upregulated under the action of various cytokines such as interferon (IFN)-γ in the tumor microenvironment. The PD-L1 on the surface of tumor cells and antigen-presenting cells binds to PD-1, continuously activating the PD-1 pathway, which can inhibit tumor antigen-specific T cell activation and weaken T cell anti-tumor activity. PD-1/PD-L1 antibodies interfere with the binding of PD-1 to PD-L1, relieving the immune suppression of this pathway and restoring T cell anti-tumor immunity ^[9]^.

The durability of the efficacy of PD-1 inhibitors is due to the memory function of the immune system. Therefore, once PD-1 inhibitors take effect, some patients achieve clinical cure, with no recurrence or progression for an extended period, leading to long-term survival ^[11]^.

As of now, the FDA has approved two PD-1 targeted immune inhibitors for second-line treatment of advanced liver cancer (namely, Nivolumab and Pembrolizumab), and one PD-L1 targeted immune inhibitor in combination with Bevacizumab for first-line treatment of advanced liver cancer (Atezolizumab). In China, Nivolumab, Pembrolizumab, and Atezolizumab have also successively received marketing approval. Among the three major domestic anti-PD-1 drugs, Sintilimab and Toripalimab have also been approved for marketing in China, with Sintilimab having been approved by the NMPA for use in combination with Bevacizumab for first-line treatment of HCC.

**1.5 Research Basis**

Liver cancer is a hypervascular solid tumor, and angiogenesis plays an important role in its growth, development, and prognosis. Angiogenic factors such as VEGF can promote tumor angiogenesis, while the disordered neovascular system can form a physical barrier, causing recruitment and infiltration obstacles for T cells; On the other hand, VEGF can induce tumor-associated immune suppression through various mechanisms, such as inhibiting the maturation of dendritic cells and promoting the activity of Tregs, MDSCs, and suppressing CTLs ^[12]^. Therefore, drugs that antagonize VEGF have a positive enhancing effect on immune responses. Moreover, the activation of immune cells can, in turn, affect tumor blood vessels, leading to their normalization. The two processes coordinate with each other, creating a mutually enhancing positive feedback loop by improving the tumor microenvironment. In addition, targeted therapies have advantages such as high specificity, rapid onset, a relatively high overall response rate, and minimal damage to normal tissues; however, the emergence of resistance limits the duration of the antitumor efficacy. Although immunotherapy has a slow onset, the duration of relief is prolonged due to the generation of memory cells ^[13]^. Tumor cell death induced by targeted drugs can enhance anti-tumor immune responses by releasing neoantigens. These provide a solid theoretical basis for the synergistic anti-tumor effects of immune checkpoint inhibitors combined with targeted drugs.

In the field of liver cancer, combination therapies of anti-angiogenic drugs and immunotherapy have shown significant survival improvement and good tolerability in advanced unresectable HCC. Currently, the combination regimen of Atezolizumab + Bevacizumab has been approved by the NMPA and FDA for first-line treatment of unresectable HCC.

Many liver cancer patients with poor HAIC outcomes often have extrahepatic metastasis and progression. Therefore, a combination treatment at this time should be a more reasonable choice. By relying on HAIC combined with systemic therapy, it can both eliminate local tumor burden and increase the concentration of antitumor drugs in the systemic circulation to delay extrahepatic progression, thereby comprehensively improving treatment efficacy.

Recently, the 2021 ASCO meeting reported a triplet therapy of Toripalimab combined with Lenvatinib and HAIC for first-line treatment of advanced hepatocellular carcinoma (NCT04044313). This study is a prospective single-arm Phase II trial that included 36 patients with advanced liver cancer who had not received systemic treatment, receiving lenvatinib in combination with toripalimab and HAIC treatment. The study results showed that after a median follow-up of 11.2 months, the median progression-free survival was 10.5 months, and the median overall survival has not yet been reached. The objective response rate (ORR) assessed according to RECIST criteria was 63.9%, and the ORR assessed according to mRECIST criteria was 66.7%, with 5 patients achieving radiological complete response. The median duration of response was 12.1 months. In addition, 8 patients were downstaged to resectable liver cancer, of which 1 underwent liver transplantation and 4 underwent curative surgical resection, with one achieving a pathological complete response. 72.2% of patients experienced grade 3-4 treatment-related adverse events (AEs), the most common being thrombocytopenia (13.9%), elevated aspartate aminotransferase (13.9%), and hypertension (11.1%) ^[14]^. Additionally, a retrospective study on lenvatinib combined with toripalimab and HAIC for first-line treatment of advanced hepatocellular carcinoma showed (Abstract e16124) that among 34 patients receiving treatment, the ORR was 84.0% (RECIST 1.1), with a CR rate of 8%. The incidence of grade 3-4 TRAEs was 28.0%. It can be seen that the triple therapy has significant therapeutic effects, and the adverse events caused by the treatment are acceptable, which may become the trend for future treatment of advanced liver cancer ^[15]^.

**1.6 Benefit-Risk Assessment**

The target population enrolled in this study consists of patients with unresectable intermediate to advanced hepatocellular carcinoma. For this type of patient, current single treatment methods have certain limitations and are difficult to meet clinical treatment needs; combination therapy is the direction for future development and breakthroughs.

Both donafenib and Sintilimab have been approved by the NMPA for the treatment of HCC. The treatment of HAIC has undergone long-term development, accumulating a wealth of clinical experience, and the technical aspects have become very mature. The combination of the three may synergistically enhance efficacy, providing greater clinical benefits to patients.

Additionally, this study will develop a detailed risk management plan to ensure that the potential harms of anticipated adverse events (AEs) to subjects are minimized. At the same time, during the treatment with the investigational drug, adverse events (AEs) and immune-related adverse events (irAEs) experienced by subjects will be closely monitored, and once relevant adverse reactions occur, the study physician will take immediate corresponding measures to ensure the safety of the subjects.

# 2 Research Objectives

## 2.1 Primary Objective

To evaluate the efficacy of donafenib combined with Hepatic Arterial Infusion Chemotherapy (HAIC) and Sintilimab as first-line treatment for unresectable hepatocellular carcinoma based on the objective response rate (ORR) (tumor assessment will be conducted using both RECIST v1.1 and mRECIST criteria, with RECIST v1.1 as the primary standard).

**2.2 Secondary Objectives**

To evaluate the efficacy and safety of donafenib combined with Hepatic Arterial Infusion Chemotherapy (HAIC) and Sintilimab as first-line treatment for unresectable hepatocellular carcinoma based on overall survival (OS), time to progression (TTP), progression-free survival (PFS), disease control rate (DCR), duration of response (DOR), changes in ECOG PS scores over time, changes in AFP levels over time, as well as adverse events and serious adverse events (tumor assessment will be conducted using both RECIST v1.1 and mRECIST criteria, with RECIST v1.1 as the primary standard).

# Research design

## Overview of the research design

This study is a single-center, open-label, single-arm, exploratory study, planning to enroll 30 cases of unresectable advanced hepatocellular carcinoma patients (see sections 4.1 and 4.2 for details).

## Sample size calculation basis

This study is an exploratory study, using a fixed sample size of 30 cases.

## Dose selection basis

### 3.3.1 Donafenib tablets

In this study, the dose of donafenib is 200mg Bid. 200mg Bid is the standard dosing regimen for donafenib in phase III clinical trials for first-line treatment of advanced hepatocellular carcinoma. An exploratory study of 6 patients with advanced gastrointestinal tumors (including 4 cases of liver cancer) treated with 100 mg Bid of donafenib combined with 240 mg Q2W of Sintilimab showed that the overall safety profile of the combination therapy was similar to that of either Sintilimab or donafenib monotherapy, with no unexpected adverse reactions occurring (data not yet published).

This study includes a safety lead-in phase, where the first 6 subjects enrolled in the study will undergo gradual safety monitoring. Each patient will receive oral administration of donafenib tablets [200 mg, Bid] combined with intravenous infusion of Sintilimab injection [200 mg, Q3W], and will receive HAIC treatment on the same day or the following day after Sintilimab infusion. The monitoring window is from the first administration of donafenib treatment to 21±3 days after the first HAIC treatment (i.e., from D1 of the donafenib monotherapy period to C2D1 of the combination therapy period). If ≥2 cases of dose-limiting toxicity (DLT) are observed among the first 6 subjects, and the research team assesses that the toxicity is solely related to donafenib treatment, the initial dose for subsequent enrolled patients receiving donafenib treatment will be adjusted to 100 mg Bid.

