### 3.3.3 Hepatic Arterial Infusion Chemotherapy (HAIC)

Based on the clinical routine experience of this research center, the FOLFOX regimen was selected for HAIC, with the following doses: Oxaliplatin 85 mg/m^2^ infusion for 2 hours, Leucovorin 400 mg/m^2^ infusion for 2 hours, 5-FU 400 mg/m^2^ bolus for 10 minutes, followed by continuous infusion of 5-FU 1200 mg/m^2^ for 23 hours. The first HAIC will be implemented on the date predetermined by the investigator, followed by once every 3 weeks (Q3W). The total number of HAIC treatments will be determined by the investigator based on the actual condition of the patient as needed.

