**Hepatic Arterial Infusion Chemotherapy**

In the chemotherapy regimen of HAIC, only the dose of oxaliplatin is adjusted. That is: when the tumor diameter > 10 cm and there is abundant blood supply, the dose of Oxaliplatin selected is 130 mg/m ^2^. For tumors ≤ 10 cm and with less abundant blood supply, the dose of Oxaliplatin selected is 85 mg/m ^2^. Additionally, when a large tumor significantly shrinks after several courses of HAIC treatment, a dose reduction may be appropriate, even down to 60 mg/m ^2^. Subsequent researchers can make appropriate dose adjustments based on the patient's actual treatment situation and tolerance, and ensure proper documentation.

***Note: If the AE can be determined to be an ADR related to one of the investigational drugs, and the investigator believes that the subject will benefit from continuing to use the other investigational drug in combination with HAIC treatment, the subject may use the other investigational drug in combination with HAIC treatment until the completion of the study treatment or the occurrence of other circumstances requiring early withdrawal/termination of the study.**

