15. During the monotherapy period of donafenib on Day 1, after calculating the number of doses for the subject based on the determined dosage, the corresponding quantity of medication will be dispensed to the subject. Subsequently, during each combination therapy period on Day 1, there is no need to retrieve any unused medication from the patient; the remaining medication can continue to be taken, and only the quantity of medication required for this treatment cycle needs to be supplemented.
16. After administering the first cycle of donafenib to the subjects on Day 1 of the monotherapy treatment period, subsequent inquiries will be made on Day 1 of each combination treatment period and at the end of the treatment period regarding the amount of medication taken in the previous cycle and the remaining amount in hand, in order to assess whether the patient's medication adherence in the previous cycle meets the requirements;
17. After the first HAIC treatment, the total number of subsequent HAIC treatments will be determined as needed by the investigator based on the actual situation of the subjects;
18. DLT assessment is applicable only to patients entering the safety induction phase of the study (i.e., the first 6 patients enrolled), with the observation and assessment period being: from the first administration of donafenib treatment to 21±3 days after the first HAIC treatment;
19. From 28 days prior to enrollment, all medications/treatments received by the subjects must be recorded in the CRF, including the generic name of the drug, administration dose, frequency, route, the reason for using the drug/treatment, and the start and end dates. Any new changes in medication treatment must be continuously updated;
20. The collection of adverse events (AEs) begins from the signing of the ICF until 30 days after the last administration or the start of a new antitumor treatment, whichever occurs first. Adverse signs, symptoms, or medical conditions that existed at the time of signing the informed consent form should be recorded as medical history;

# Appendix 14

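### The six-patient safety lead-in does not say which oxaliplatin level it uses, so the 130 mg/m² level may reach later patients with no or only one DLT-observed patient

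*Protocol*

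**What the plan says.** **Lead-in.** Section 3.3.1 (and the Administration dose row of the Protocol Summary) says that "the first 6 subjects enrolled in the study will undergo gradual safety monitoring". It fixes donafenib at 200 mg bid and sintilimab at 200 mg Q3W. For HAIC, section 3.3.1 adds only "and will receive HAIC treatment on the same day or the following day after Sintilimab infusion".

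**Window.** "The monitoring window is from the first administration of donafenib treatment to 21±3 days after the first HAIC treatment", which covers one HAIC course.

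**Rule.** There are two conditions. One is a count: "If ≥2 cases of dose-limiting toxicity (DLT) are observed among the first 6 subjects". The other is attribution, which requires that "the research team assesses that the toxicity is solely related to donafenib treatment". If both hold, later patients start donafenib at 100 mg bid. Section 5.3 repeats the rule for donafenib. No other consequence of a lead-in DLT is stated.

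**Who is observed.** Attachment 1, note 18: "DLT assessment is applicable only to patients entering the safety induction phase of the study (i.e., the first 6 patients enrolled"). Sections 6.2 and 6.3 say the same.

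**Oxaliplatin as a single dose.** Section 3.3.3 gives HAIC "with the following doses: Oxaliplatin 85 mg/m^2^ infusion for 2 hours". The HAIC part of section 5.2 and the Administration dose row agree on 85 mg/m².

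**Oxaliplatin by tumor.** The HAIC part of section 5.3 says that "when the tumor diameter > 10 cm and there is abundant blood supply, the dose of Oxaliplatin selected is 130 mg/m"². It assigns 85 mg/m² to tumors of 10 cm or less with less abundant supply. The Dose adjustment scheme row of the Protocol Summary says the same.

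**The concern.** The regimen has either one oxaliplatin level or two, depending on which section is read, and the lead-in does not say which applies to it. The condition for 130 mg/m² is a tumor characteristic that can already be met at the first HAIC. Large tumors are in scope: section 1.2 presents HAIC as well suited to them, and the eligibility criteria set no size limit.

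The lead-in holds the protocol's only numerical safety rule for the triplet. The earlier combination experience cited in 3.3.1 is six patients on a lower donafenib dose with sintilimab, and HAIC is not mentioned there. If the lead-in includes few or no patients at 130 mg/m², a clean result says almost nothing about the triplet at that level, yet later patients may receive it without DLT observation. A report that calls the lead-in uneventful, without giving the oxaliplatin doses, would invite a wider conclusion than the data carry.

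**Working it through.** The protocol gives no operating characteristics for the lead-in, so there is no stated figure to reproduce.

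**Step 1: the dose passages side by side.** The ratio of the two levels is 130 / 85 = 1.53.

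| Tumor | Supply | Sections 3.3.3 and 5.2 | Section 5.3 |
|---|---|---|---|
| > 10 cm | abundant | 85 | 130 |
| ≤ 10 cm | less abundant | 85 | 85 |
| > 10 cm | less abundant | 85 | not assigned |
| ≤ 10 cm | abundant | 85 | not assigned |

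Section 5.3 also allows a reduction to 60 mg/m² after several courses. That falls outside the DLT window and plays no part here.

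**Step 2: lead-in at 85 mg/m² only.** The number DLT-observed at 130 is 0 of 6 with certainty.

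**Step 3: section 5.3 applies from the first HAIC.** Let s be the share of patients who receive 130. The protocol does not give s, so 10% to 40% is an assumption, as is enrollment order unrelated to tumor type. The number at 130 among six is then Binomial(6, s):

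- P(none) = (1 − s)⁶
- P(at most one) = (1 − s)⁶ + 6s(1 − s)⁵
- Expected number at 130 among the later 30 − 6 = 24 patients = 24s

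| s | P(none of 6) | P(at most 1 of 6) | 24s |
|---|---|---|---|
| 10% | 53% | 89% | 2.4 |
| 20% | 26% | 66% | 4.8 |
| 30% | 12% | 42% | 7.2 |
| 40% | 5% | 23% | 9.6 |

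For example, at s = 20%, 0.8⁶ = 0.262 and 6 × 0.2 × 0.8⁵ = 0.393, which sum to 0.655.

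**Step 4: what a clean result would show.** With zero DLTs in k patients, the one-sided exact 95% upper bound on the DLT rate is 1 − 0.05^(1/k).

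- k = 1: 1 − 0.05 = 95%
- k = 2: 1 − 0.05^(1/2) = 78%
- k = 6, if all six were at one level: 1 − 0.05^(1/6) = 39%

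**Step 5: following a DLT through the rule.** A DLT at either oxaliplatin level adds one to the same count. Reaching two does not lower donafenib by itself, because the toxicity must also be judged solely related to donafenib. DLTs attributed to HAIC, or to the combination, fail that second condition, and the protocol states nothing further for them.

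**The case against.** The best defense is that the lead-in is about donafenib. It sits under the donafenib dose basis, its one rule sets the donafenib starting dose, and section 3.3.3 rests HAIC dosing on the center's routine experience. In the Administration dose row, the lead-in note directly follows the HAIC definition at 85 mg/m², so 85 is a natural reading. Safety oversight also continues for all 30 patients: checks before each cycle, AE and SAE reporting, tolerance-based oxaliplatin adjustment, and the investigator's power to stop the study. All of this stands. It means that nothing in the protocol says the lead-in formally clears a HAIC dose, and that later patients are not unmonitored. It does not settle which level the lead-in uses. If 85 is meant, it confirms that 130 mg/m² is not DLT-observed at all.

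A reader might go further and infer that toxicity at 130 mg/m² would wrongly drive donafenib down, or that patients at 85 mg/m² would mask it. The documents support neither. The sole-attribution condition stands between a HAIC-related DLT and a donafenib change. The threshold is an absolute count of two, so a DLT at 130 counts in full whoever else is in the six. Nor can the effect of a mixed group on the count be sized from this protocol, which gives no DLT rate by oxaliplatin level.

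It is also an inference, not a statement in section 5.3, that 130 mg/m² applies from the first course. The passage sits under dose adjustment. Both readings are therefore worked above.

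**Conclusion.** The point holds as a contradiction between dose passages with a direct effect on what the lead-in can show. Under the 85-only reading, no patient is DLT-observed at 130 mg/m². Under the tumor-based reading, the probability of at most one such patient is 89% to 23% over assumed shares of 10% to 40%, with about 2 to 10 later patients expected at that level. A clean result in one or two patients leaves an upper bound of 95% or 78%. These probabilities depend on the assumed share and on enrollment order being unrelated to tumor type.

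A separate gap follows from the wording of the rule: DLTs not attributed solely to donafenib have no stated consequence. No view is taken on which oxaliplatin dose is right. The matter should be corrected, but it does not undermine the ORR analysis.

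**What to change.** 1. The sponsor and investigators should reconcile the Administration dose row, 3.3.3 and 5.2 with the Dose adjustment scheme row and 5.3, including the two tumor combinations that 5.3 leaves unassigned.
2. State in 3.3.1 which oxaliplatin level or levels the lead-in includes.
3. Record the oxaliplatin dose given with each DLT assessment, and tabulate lead-in DLTs by that dose.
4. State that the lead-in's safety conclusion applies only to the level or levels actually received in it.
5. Settle in the same reconciliation whether DLT observation should continue for a level not represented among the six, and what follows from DLTs not attributed solely to donafenib. Both are clinical decisions, and no rule is proposed here.

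The cost of items 1 to 4 is minor wording changes and one added field on the DLT form, with no extra patients or visits. Any cost of item 5 depends on what the investigators decide.
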